### Ethical considerations

Approvals for the study have been obtained from the Ethics Committees of the London School of Hygiene & Tropical Medicine (Ref: 29839), Kintampo Health Research Centre, Ghana (Ref: KHRCIEC/2024‐01) and the Ghana Health Service (Ref: GHS‐ERC: 024/11/23). Regulatory approval has also been obtained from the Ghana Food and Drug Administration (Ref: FDA/247). The trial will be externally monitored and an independent data safety and monitoring board will oversee participant safety and evaluation of the results.

### Study procedures

#### Stakeholders' engagement and community sensitisation

The study team has met with the Programme Managers and National Coordinators of the SMC and NTD programmes of the Ghana Ministry of Health, as well as with the regional and district Education directors and supervisors, to seek their collaboration and partnership in the implementation of this study. Community sensitisation and engagement meetings will be organised prior to the commencement of the study to explain the nature of the study to the parents/caregivers of potentially eligible children.

##### Pre‐intervention stage

After written informed consent has been obtained from a parent/caregiver 1 day before the planned start date of the pre‐intervention survey, along with a positive assent from children aged ≥7 years when required, a pre‐labelled stool collection container will be provided to the parent/caregiver. The parent/caregiver will be encouraged to collect stool from their child and keep this safely for the research team who will visit them the following day, when a purpose‐designed electronic questionnaire will be administered to the parent/caregiver. The questionnaire will cover information such as socio‐demographic, health and residence characteristics, history of deworming and malaria treatment. Height/length (cm) and weight (kg) of each child will be measured and anthropometric indices height‐for‐age, weight‐for‐age, weight‐for‐height and body mass index, will be calculated using the WHO AnthroPlus software (www.who.int/growthref/tools/en/). Each study participant's household will be mapped with global‐positioning system (GPS) coordinates obtained with a hand‐held GPS device. Finger‐prick blood samples will be collected from each child participant for thick and thin smear examination for malaria microscopy, and blood spot filter papers will be collected for DNA isolation and polymerase chain reaction (PCR) amplification for species determination. Hb concentrations will be measured using the Haemocue® method. Freshly voided urine samples will be collected from all study children. Urine filtration test will be used to quantify *Schistosoma(S) haemotobium*, according to standard guidelines [20]. Parallel testing for circulating cathodic antigens (CCA) will be used to complement the filtration test. The urine CCA dipstick test has been extensively used in SSA and had sensitivity and specificity values for *Schistosoma mansoni* ranging from 52.5% to 63.2% and 57.7% to 75.6%, respectively [21]. Stool samples will be collected to detect intestinal helminths. Duplicate Kato‐Katz thick smears will be prepared from the stool samples and examined by experienced technicians using light microscopy to determine the egg counts for *S. mansoni* and STH. The numbers of eggs per slide will be used to obtain a measure of the number of helminth eggs per gramme of faeces (EPG). The intensity of the helminth infection will be categorised according to standard guidelines [20]. A multiplex PCR assay will also be used for simultaneous detection of mixed infections of helminths [22]. Quality control will be performed by re‐examining at least 10% of randomly selected blood slides, urine filters and Kato‐Katz smears by an experienced independent laboratory scientist. Laboratory staff performing the analyses will be masked to the origin of samples.

##### Intervention stage

Given that the focus of this project is to evaluate the effectiveness of the integrated SMC‐MDA control programmes, the first day of starting the intervention stage (Day 0) will correspond to the day prior to the commencement of the first cycle of SMC in the study area. On Day 0, the communities will be randomised at community level into two clusters at 1:1 ratio to receive either combined SMC and anthelminthic drugs (intervention cluster) or SMC drugs only (control cluster). Given that 4‐aminoquinoline drugs are reported to have antagonistic pharmacological interactions with PZQ [23], the SMC partner drugs, AQ (a 4‐aminoquinoline derivative) and SP will not be administered with anthelminthic drugs (ALB and PZQ) on the same day in this study. Therefore, eligible children randomised into the intervention clusters will receive ALB and PZQ on Day 0 and those randomised into the control clusters will receive vitamin A and zinc supplement as control drugs on this day. On the following day, which corresponding to the start (Day 1) of the first SMC cycle, the children in the control and intervention clusters will receive SPAQ according to the WHO and Ghana SMC implementation guidelines. This will be followed on the second and third day of the SMC cycle with all study children in the two groups receiving AQ, in line with the SMC guidelines [5]. The study will administer AQ on Days 2 and 3 to the children in the presence of their parents/caregivers. Trained field workers will visit all enrolled children daily, irrespective of the study arms, at home starting from the evening of Day 0 till 3 days after completion of the first cycle of SMC course, using a purpose‐designed electronic diary card, to collect adverse drug reactions and adverse events such as vomiting, skin rash, body weakness, etc. Trained research assistants will visit each child 1 month after each round of SMC cycle to check that there are no severe reactions to the previous treatment and to give the next round of treatment (Table 1).

**TABLE 1 tmi14062-tbl-0001:** Schematic diagram of the study procedures for the effectiveness study.

SMC cycle	1					2, 3 and 4	End of malaria season (i.e., 1 month after completion of the last SMC cycle)
Timelines (days)	Pre‐intervention survey	Day 0	Day 1	Days 2 and 3	Days 4–6		Post‐intervention survey
Study procedures						Passive surveillance involving collection of cases of breakthrough clinical malaria during the monthly cycle of SMC drugs administration according to WHO guidelines till the end of the malaria season	
Informed consent ± assent	X						
Enrolment and questionnaire administration to parents/caregivers	X						
Distribution of collecting bottles for stool sample a day preceding sample collection day.	X						
Sample collection (finger‐prick blood, urine, stool samples)	X	X					
Randomisation and intervention		X					
Intervention villages: SMC + anthelminthics		ALB + PZQ	AQ + SP	AQ			
Control villages: SMC + placebo		Vit A + Zn	AQ + SP	AQ			
Safety assessments (active surveillance)		X	X	X	X		
Post‐intervention survey							X
Sample collection: Finger‐prick							X
Sample collection: stool							X
Sample collection: urine							X

Abbreviations: ALB, albendazole; AQ, amodiaquine; PZQ, praziquantel; SMC, seasonal malaria chemoprevention; SP, sulphadoxine‐pyrimethamine Vit A, vitamin A; Zn, zinc.

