### Sample size determination

We assumed that the mean Hb concentration in the SMC alone group will be 10.5 g/dL with a standard deviation of 1.5 g/dL [3]. Assuming an intra‐class correlation coefficient of 0.05, then 10 communities per cluster, a study of 60 children per community will have 80% power to detect an increase in mean Hb of 0.5 g/dL (to 11.0 g/dL) in the SMC plus anthelminthic group as statistically significant at 5% level. A minimum sample size of 1200 school‐age children (5–10 years) will be enrolled. This study will be implemented in three stages: pre‐intervention, intervention and post‐intervention. The pre‐intervention survey will be conducted to determine the prevalence of malaria‐helminth co‐infection in the study population.

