#### Sampling for the intervention stage of the trial

There will be two study arms in the intervention phase of this trial—intervention and control arms. Ten schools within Pru East communities will be randomised to the intervention arm and another 10 schools will be randomised to the control arm. As calculated above, a minimum of 60 children who satisfy all eligibility criteria will be enrolled sequentially in each of the 10 schools randomised into the intervention and control arm, respectively. To identify these children, we will undertake a census of all children aged 5–10 years in the communities selected for the intervention stage of the trial. Subsequently, we will use a sampling frame for random sampling from the census list to enrol the required number of children into each study arm. We will keep a reserve list of potentially eligible children in case of any refusals from the sampling list.

Data collection for the cost‐effectiveness analyses will involve semi‐structured interviews with key informants from the regional and district education and health offices, using purposive sampling to select health facility personnel, community health workers (CHWs) and school teachers involved in the delivery of SMC with or without MDA for helminths. Approximately 6–12 interviews are anticipated at the regional and district level, up to 10 with health facility personnel, 10–15 with CHWs and 10–20 with school teachers. Key informants will be chosen to reflect maximum expected variation across the study area, for example, a mix of urban and rural communities, distance from the district centre, etc. This flexible and purposive approach to sampling is a standard and important feature of economic evaluations.

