For the cost‐effectiveness analysis (CEA), the main measure of the effects will be disability‐adjusted life‐years (DALYs) averted. DALYs combine mortality (years of life lost [YLLs]) and morbidity (years lived with disability [YLDs]) into a single measure of effect, allowing the impact of SMC with MDA to be compared with the impact of different types of health interventions. The effect measure used to calculate DALYs will be moderate and severe anaemia cases averted (where anaemia as the primary outcome for the CEA, which is where the main incremental health benefit from co‐delivery is expected), derived from unadjusted results of the trial, calculated on the basis of intention‐to‐treat (ITT). DALYs will be modelled using a 3% discount rate in the base case, no age weighting, standard DALY weights and life tables [26], and other secondary data (e.g., duration of an episode of anaemia) [27]. The CEA results will be expressed as an incremental cost‐effectiveness ratio (ICER). The ICER is calculated as the difference in costs between MDA + SMC versus SMC alone, divided by the difference in effects between those strategies (Figure 2).
$$\text{ICER}=\frac{\text{cost of administering}\;\mathrm{MDA}+\mathrm{SMC}\text{(intervention)}-\text{cost of administering}\;\mathrm{SMC}\text{(control)}}{\left(\text{DALY averted in intervention}\;\mathrm{arm}-\text{DALYs averted in control}\;\mathrm{arm}\right)}$$

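### With 10 communities per arm, no restriction on the 1:1 allocation is described and the cost-effectiveness effect is fixed as unadjusted, so baseline Hb and infection data collected before treatment are not used where chance imbalance matters most

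*Protocol article*

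**What the plan says.** **Allocation.** The Intervention stage section states that on Day 0 "the communities will be randomised at community level into two clusters at 1:1 ratio". The section on sampling for the intervention stage gives the number: 10 schools go to the intervention arm and "another 10 schools will be randomised to the control arm". Neither section, nor Table 1, mentions stratification, matching or constraint. Neither calls the randomisation simple or unrestricted.

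**Data available beforehand.** The Pre-intervention stage section and Table 1 place a survey before Day 0 that measures Hb, malaria and helminths. Its stated purpose, under Sample size determination, is descriptive: a pre-intervention "survey will be conducted to determine the prevalence of" malaria-helminth co-infection. The sampling section gives 15 children per school as an example.

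**Analysis.** The primary endpoint is change in Hb from inclusion to the post-intervention survey. The Statistical analysis plan section adjusts odds ratios for sex, age group, weight and baseline malaria and helminth infection. Baseline Hb and community-level variables are not in that list. The section on data collection for the cost and cost-effectiveness analyses takes moderate and severe anaemia cases averted, the effect behind the DALYs, as "derived from unadjusted results of the trial", on an intention-to-treat basis.

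**The concern.** Randomising 20 units does not reliably balance community characteristics. Two of these bear directly on the outcome. Community Hb level is a baseline value of the endpoint. Helminth burden is what the added drugs act on, so it can affect both the course of Hb and the benefit that can be achieved.

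The plan collects both before treatment. As described, it uses neither to balance the allocation, and it excludes both from the estimate that enters the denominator of the cost-effectiveness ratio. At stake are the precision and credibility of that estimate. With a visible baseline gap, a reader of the economic result could not tell how much of the anaemia difference was there at the start.

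**Working it through.** **Inputs, all from Sample size determination unless stated.** Control mean Hb "will be 10.5 g/dL with a standard deviation of 1.5 g/dL"; intra-class "correlation coefficient of 0.05"; 10 communities per arm; 60 children per community; target difference 0.5 g/dL; two-sided 5% (Statistical analysis plan); 15 survey children per school (sampling for the pre-intervention stage, an example).

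**1. The plan's own figure.** The plan states that "a study of 60 children per community will have 80% power to detect an increase in mean Hb of 0.5 g/dL".
- Design effect = 1 + (60 − 1) × 0.05 = 3.95.
- Effective n per arm = 600 / 3.95 = 151.9.
- SE of the arm difference = 1.5 × √(2 / 151.9) = 0.172 g/dL.
- Power = 82.8% by the normal approximation and 78.4% with a t distribution on 18 degrees of freedom. The stated 80% lies between the two and is sound.

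**2. Chance imbalance in community mean Hb if allocation is unrestricted.** This applies the planning ICC to baseline Hb.
- Between-community SD = 1.5 × √0.05 = 0.335 g/dL.
- SD of the arm difference = 0.335 × √(2/10) = 0.150 g/dL.
- P(gap above 0.20) = 18%; P(gap above 0.25) = 9.6%.
- With ICC 0.02 or 0.10 (assumed range), the SD is 0.095 or 0.212 g/dL.

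**3. How this relates to the SE.** The squared SE, 0.172² = 0.0296, is the sum of a between-community part, 0.150² = 0.0225, and a within-community part, (2/10) × 2.25 × 0.95 / 60 = 0.0071. The imbalance in step 2 is therefore the larger component of an error that the power calculation already counts.

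**4. What it could do to an unadjusted anaemia difference.** Assume normal Hb with SD 1.5, and a baseline gap that persists in full to follow-up (an upper bound). The cut-off is the article's 11 g/dL, because limits for moderate and severe anaemia are not given.
- Target effect: P(Hb < 11) falls from 63.1% (mean 10.5) to 50.0% (mean 11.0), or 13.1 points.
- A gap of 0.15 g/dL, centred on 10.5, shifts the difference by 3.8 points (29% of 13.1).
- A gap of 0.25 g/dL shifts it by 6.3 points (48% of 13.1).

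**5. What constrained allocation would gain.** Reliability of a survey mean of m children is R = m × ICC / (1 + (m − 1) × ICC), and the residual SD is 0.150 × √(1 − R).

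| Children measured per community | R | Residual SD (g/dL) | P(gap > 0.20) | P(gap > 0.25) |
|---|---|---|---|---|
| None used | – | 0.150 | 18% | 9.6% |
| 15 | 0.44 | 0.112 | 7% | 2.6% |
| 60 (assumes all are measured before allocation) | 0.76 | 0.074 | 0.7% | 0.1% |

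Simulated constrained randomisation, drawing from the best-balanced 10% of allocations, gave SDs of 0.112 and 0.075, in agreement.

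**6. Helminth prevalence.** The documents give no between-community SD. If it were 10, 15 or 20 points (assumed), the chance of an arm gap above 10 points would be 3%, 14% or 26%.

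**The case against.** The case against is substantial, and most of it stands.

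- **Unrestricted allocation is not stated.** A reader might infer plain randomisation, but the article gives only unit, ratio and day. A condensed article may leave stratification or constraint to the full protocol. The text supports only that no restriction is described.
- **Chance imbalance is not bias.** A reader might infer a biased estimate. Under randomisation the imbalance is random error, and step 3 shows that it is already in the SE. An unadjusted randomised comparison is a valid estimator.
- **The later analysis does correct part of it.** A change in Hb removes a stable difference in level. The anaemia endpoint is also framed as a change in prevalence. Adjusting for each child's baseline infection captures much of a community gap in infection. If the economic effect were taken from the change in prevalence, step 4 would overstate the shift.
- **The imbalance is only partly avoidable.** With 15 children per school about 56% of the variance remains. The article does not say that all 20 trial communities will have a survey mean, or that laboratory results will be ready by Day 0.
- **Sensitivity analyses are planned.** The economic analysis will vary effectiveness measures. That shows how the ratio responds to a different effect, but it does not recentre an estimate that started from unequal arms.

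What remains does not rest on silence. The cost-effectiveness effect is expressly unadjusted, although baseline data are collected and adjusted estimates are planned elsewhere in the article.

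**Conclusion.** The point holds as a worthwhile improvement, not as an error in the design. The sample size stands.

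If allocation is unrestricted, the arms' community mean Hb differs by chance with an SD of 0.15 g/dL, and the gap exceeds half the target effect with probability 9.6%. The primary change-in-Hb analysis is partly protected. The unadjusted anaemia effect behind the DALYs is the most exposed: a one-SD gap could move it by up to about 3.8 points against a target of 13.1.

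These figures assume that the planning ICC applies to baseline Hb. The anaemia figures also assume normal Hb, full persistence of the gap and the 11 g/dL cut-off, since the shift for moderate and severe anaemia cannot be computed from the article. The part about the economic effect rests on explicit text. The part about allocation depends on what the full protocol says.

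**What to change.** 1. **Cost-effectiveness section.** Derive the anaemia cases averted from a cluster-aware model adjusted for baseline Hb (or anaemia) and baseline infection, expressed as an absolute risk difference so that it converts to cases. Report the result beside the unadjusted intention-to-treat effect. This uses data already collected, costs a few lines of text and one further model, and remains possible after allocation.

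2. **Intervention stage section.** State whether allocation is restricted. If it is not, and survey results for all 20 communities are available before Day 0, use stratified or covariate-constrained randomisation on community mean Hb and helminth prevalence. Draw at random from a large set of acceptable allocations, and include the balancing variables in the analysis. The cost is a short allocation program, survey results on time, and one or two of the 18 degrees of freedom. If helminth results would be late, balancing on Hb alone still gives the gain shown for Hb.

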##### Post‐intervention stage

All child participants enrolled in the intervention study will be evaluated 1 month after the last course of SMC, which corresponds to the end of malaria transmission season, to measure their Hb concentration and to obtain a further blood film, dried blood spot, stool and urine samples, to test for malaria‐helminth co‐infections using parasitological methods such as microscopy, Kato‐Katz, urine filtration test and improved diagnostic tools including molecular methods (quantitative polymerase chain reaction), as described above.

##### Data collection for the cost and cost‐effectiveness analyses

The incremental financial and economic costs of delivering the integrated SMC‐MDA programme in the intervention stage of this study will be estimated from a provider (Government of Ghana and donor) perspective, and compared to the counterfactual of giving SMC drugs alone. Financial cost data (direct expenditure on intervention delivery) and economic costs (donated goods or services, such as time of salaried health workers and schoolteachers) will be collected through review of project records and semi‐structured key informant interviews (KIIs) at district, health facility, CHW and school levels. Detailed costs will be captured for disaggregated cost categories, including SMC and MDA drugs; drug supply chain; school teacher delivery of doses; supervision; training; planning meetings; sensitisation; and supplies. Incremental costs required for the integrated delivery of MDA with SMC above what would be required for SMC delivered alone will be identified. The cost of diagnosis and treatment of moderate and severe anaemia from the health service perspective will be estimated using a combination of primary and secondary data. Cost per outpatient visit and cost per inpatient day (excluding diagnosis and treatment) will be obtained from existing data sources [24, 25]. Costs of diagnostic tests, medicines and provider time for treating cases of moderate and severe anaemia will be captured through KIIs with health staff at facilities providing outpatient and inpatient services in the study area. These parameters will be used to estimate incremental cost savings due to cases of moderate and severe anaemia averted by SMC plus MDA compared to SMC alone.

For the cost‐effectiveness analysis (CEA), the main measure of the effects will be disability‐adjusted life‐years (DALYs) averted. DALYs combine mortality (years of life lost [YLLs]) and morbidity (years lived with disability [YLDs]) into a single measure of effect, allowing the impact of SMC with MDA to be compared with the impact of different types of health interventions. The effect measure used to calculate DALYs will be moderate and severe anaemia cases averted (where anaemia as the primary outcome for the CEA, which is where the main incremental health benefit from co‐delivery is expected), derived from unadjusted results of the trial, calculated on the basis of intention‐to‐treat (ITT). DALYs will be modelled using a 3% discount rate in the base case, no age weighting, standard DALY weights and life tables [26], and other secondary data (e.g., duration of an episode of anaemia) [27]. The CEA results will be expressed as an incremental cost‐effectiveness ratio (ICER). The ICER is calculated as the difference in costs between MDA + SMC versus SMC alone, divided by the difference in effects between those strategies (Figure 2).
$$\text{ICER}=\frac{\text{cost of administering}\;\mathrm{MDA}+\mathrm{SMC}\text{(intervention)}-\text{cost of administering}\;\mathrm{SMC}\text{(control)}}{\left(\text{DALY averted in intervention}\;\mathrm{arm}-\text{DALYs averted in control}\;\mathrm{arm}\right)}$$

**FIGURE 2 tmi14062-fig-0002:**
[figure not shown]
Schematic design of the study. DALY, disability‐adjusted life‐years; MDA, mass drug administration; SMC, seasonal malaria chemoprevention.

